#### Assessment of causality

The relationship of each adverse event to the trial procedures, conduct or intervention must be determined by a medically qualified individual according to the following definitions:

Related: the adverse event follows a reasonable temporal sequence from the trial procedures, conduct or intervention. It cannot reasonably be attributed to any other cause.

Not related: the adverse event is probably produced by the participant’s clinical state or by other modes of therapy administered to the participant.

#### Procedures for reporting adverse events

It is the responsibility of the local investigator to ensure that all adverse events considered related to the intervention and occurring during the course of the study are recorded. This will include but not be limited to:A description of the eventThe dates of the onset and resolutionAction takenOutcomeAssessment of relatedness to the trial procedures, conduct or interventionWhether the AE is serious or not

Whether the AE arises from errors in OrganOx *metra*^*®*^ device functioning or use, adverse events that occur during the course of the study should be treated by established standards of care that will protect the life and health of the study subjects.

Adverse events considered related to the intervention should be recorded on the eCRF via the MACRO database provided. If the eCRF is unavailable for any reason, a paper version of the form should be completed.

The severity of events will be assessed on the following scale: 1 = mild, 2 = moderate, 3 = severe.

Non-serious AEs, considered related to the trial procedures, conduct or intervention as judged by a medically qualified investigator or the sponsor, will be followed up until resolution.

#### Reporting procedures for serious adverse events

It is the responsibility of the local investigator to ensure that all adverse events which fall in to the category of serious adverse events (SAEs) are reported to NHSBT Clinical Trials Unit, chief investigator, central investigators and, if required, to their local R&D department as soon as possible after becoming aware of the event but no later than 24 h. This will include but not be limited to:A description of the eventThe dates of the onset and resolutionAction takenOutcomeAssessment of relatedness to the trial procedures, conduct or intervention

Serious adverse events will be collected from transplant until 6 months following the transplant, via a purposely designed MACRO database (access via www.ctu.nhsbt.nhs.uk/macro). SAEs will be automatically notified to NHSBT CTU. If the eCRF is unavailable for any reason, a paper version of the form should be completed, scanned and emailed to [contact]. Within the following five working days, the local investigator may be required to provide additional information on the SAE in the form of a written narrative. This should include a copy of the completed SAE form, and any other diagnostic or relevant information that will assist the understanding of the event.

Additional and further requested information (follow-up or corrections to the original case) should also be added to eCRF using a new SAE Report Form. NHSBT CTU will ensure that all SAEs are reported to the sponsor.

The clinical reviewers will review the SAEs and, if they agree that the SAEs are unexpected and related, or pose an immediate risk to patient health or safety, then they will report them to the DMC immediately and to the device manufacturer and the REC within 15 calendar days of the chief investigator becoming aware of the event. The DMC will review the accumulating data at regular intervals.

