#### Anticipated adverse events

As liver transplant recipients, all recruits to the DeFat trial are at high risk of experiencing AEs due to the complexity of their condition. Many of these events are anticipated as a result of the patient’s medical condition and standard treatment received in hospital. We will only document adverse events if in the opinion of the investigator they are likely to be associated with the trial intervention.

All adverse events meeting the definition of serious adverse event will be recorded.

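### The two causality classes leave no place for a possibly related SAE, so one judged to pose no immediate risk misses the expedited report to the DMC, device manufacturer and REC

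*Protocol article*

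**What the plan says.** Under Assessment of causality, the relationship of each event to the trial "must be determined by a medically qualified individual according to the following definitions". There are two definitions. *Related* needs a reasonable temporal sequence and a second condition: "It cannot reasonably be attributed to any other cause". *Not related* means that "the adverse event is probably produced by the participant’s clinical state", or by other treatment the participant received. There is no intermediate class.

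Under Reporting procedures for serious adverse events, the site sends every SAE, with its own assessment of relatedness, to the trials unit, the chief investigator and the central investigators within 24 h. The trials unit passes all SAEs to the sponsor. The clinical reviewers then look at these reports. The condition for sending one onward is "if they agree that the SAEs are unexpected and related, or pose an immediate risk to patient health or safety". Where it is met, the DMC is told at once, and the manufacturer and REC no later than 15 calendar days after the chief investigator learns of the event. The same section says that the DMC reviews accumulating data at regular intervals. Safety reporting adds a DMC review after the first ten perfusions.

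Under Anticipated adverse events, the article says that "all recruits to the DeFat trial are at high risk of experiencing AEs due to the complexity of their condition".

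**The concern.** The expedited route uses the word *related*, so it inherits that word's definition. The definition asks the assessor to exclude every other reasonable cause. In liver transplant recipients that is seldom possible: the article itself calls them a high-risk group. Its Background also links moderate to severe steatosis, which is the entry condition for the donor livers, to a 71% increase in the risk of graft loss. A competing explanation will often be at hand.

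The section also leaves the decision to the clinical reviewers. Nothing in it says that a site's assessment of related stands if the reviewers take another view.

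What is at stake is how soon an independent body sees a possible safety signal. The Objectives describe this as the first clinical study of the defatting protocol and make safety part of the primary objective. The only DMC review fixed by number comes after ten perfusions, which leaves 60 − 10 = 50 planned livers to later reviews whose timing the article does not fix.

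**Working it through.** No figure in the plan bears on this point, so the check compares the definitions with the escalation rule.

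**Step 1: do the two classes cover every SAE?** Take an SAE that follows the intervention in a reasonable temporal sequence, and ask how strong the other explanation is.

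- No other cause is reasonable: the event is *related*.
- Another cause is probable: the event is *not related*, even if the intervention may also have contributed.
- Another cause is reasonable but not probable: the event fails *related* because of "It cannot reasonably be attributed to any other cause", and it fails *not related* because that class needs the other cause to be probable. It belongs to neither.

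The classes are therefore not exhaustive. In the second and third cases alike, an SAE for which the intervention is a plausible but not the only explanation cannot be called *related*.

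**Step 2: apply the escalation rule.** There are two alternative triggers. One needs the event to be both unexpected and related. The other needs an immediate risk and says nothing about relatedness.

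- The reviewers judge the SAE unexpected and related: expedited report.
- The site judges it unexpected and related, the reviewers do not, and no immediate risk is seen: no expedited report.
- The link is possible, another cause is reasonable, and no immediate risk is seen: no expedited report.
- The link is possible, another cause is reasonable, and the reviewers see an immediate risk: expedited report.

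**Step 3: what still happens to an SAE that misses the expedited route?** It is recorded, reported within 24 h to the trials unit, chief investigator and central investigators, and passed to the sponsor. The DMC meets it at the review after ten perfusions or at a later periodic review. What is lost is the immediate report to the DMC and the 15-day report to the manufacturer and REC.

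**Step 4: compare with non-serious events.** Procedures for reporting adverse events says that those considered related "as judged by a medically qualified investigator or the sponsor, will be followed up until resolution". There, either party's judgement is enough. The action differs, follow-up rather than expedited reporting, so this is not a contradiction. It does show that the article already uses an either-party rule for less serious events.

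**The case against.** The strongest reply is that the safety net is wider than this one rule. The immediate-risk trigger needs no relatedness. Every SAE reaches the trial's central team within 24 h whatever its cause. Incident reporting to the manufacturer and to NHSBT runs in parallel. The sponsor must suspend the study on suspicion of unacceptable risk. Graft and patient survival, primary non-function and vascular complications are collected for transplanted recipients without any causality filter. All of this stands, and it limits the point to a delay in independent review.

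A second reply is that *agree* may mean that the reviewers agree among themselves, and that they review all SAEs, not only those the site called related. On that reading a site's *related* is not required, and the reviewers can already upgrade an event. This stands too. On either reading, however, a site's *related* is not sufficient.

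A third reply is that this is a condensed article and that the full protocol or the DMC charter may say how disagreements are settled. Silence on that alone would not be a finding. The causality definitions and the trigger, though, are stated in full, and the gap lies in what they say.

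A reader might go further and infer that uncertain events in treated livers are never escalated, or that primary non-function, hepatic artery thrombosis or graft loss would go unreported. The documents do not support this. The immediate-risk trigger may catch such events, and the rule covers both arms. These are also prespecified outcomes, so if they missed the first trigger it might be because they count as expected, which is a separate matter from causality.

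**Conclusion.** The point holds in a limited form. The two causality classes are not exhaustive, and *related* is set so strictly that an SAE with any other reasonable cause cannot meet it. Possibly related SAEs, and SAEs that the reviewers downgrade, miss expedited reporting under this section when they are judged to pose no immediate risk. They reach the DMC only at a scheduled review. No SAE goes unrecorded, and none is withheld from the trials unit, investigators or sponsor.

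No size can be put on the delay or on the number of events. That would need the rate of such SAEs, the number of reviewers and how often assessors differ, none of which the article gives. The conclusion rests on reading the definitions literally and on taking the relatedness assessment in the site's SAE report as the local investigator's, since the causality section names only a medically qualified individual. It should be corrected because safety is part of the primary objective of a first clinical study, but it does not undermine the trial.

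**What to change.** Two edits.

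- In Assessment of causality, define *related* as a reasonable possibility that the trial's procedures, its conduct or the intervention caused or contributed to the event, and *not related* as the absence of such a possibility. Every event then falls into exactly one class.
- In Reporting procedures for serious adverse events, let the judgement of either the local investigator or a clinical reviewer suffice for *related*. A reviewer may upgrade the site's assessment but not downgrade it, and disagreements go forward with both opinions. Leave the immediate-risk trigger as it is.

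The condition that the event be unexpected is not changed by these edits, so events treated as expected would still depend on the immediate-risk trigger.

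The cost is a few sentences of text and a few more expedited reports from at most 60 recipients, some of which will prove unrelated.

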### Frequency and plans for auditing trial conduct {23}

The investigators shall conduct this study in accordance with this protocol and any conditions of approval/notification imposed by the Research Ethics Committee and Competent Authority. Failure to comply with and/or inability to meet these regulations may jeopardise further participation of the investigator or investigative site in this and future clinical studies.

A ‘protocol deviation’ is a failure to adhere to the requirements specified in this study protocol without adequate justification. Examples may include the enrolment of a liver or recipient not meeting all of the inclusion/exclusion criteria specified in section 8 or missed study procedures without documentation. Livers excluded after randomisation due to factors not known at the time of randomisation (see procedures for reporting adverse events) will not be deemed protocol deviations.

#### Reporting of protocol deviations

All protocol deviations must be recorded and reported to the data monitoring committee. The DMC will review all deviations and assess their impact on patient safety. Serious breaches must be reported (see procedures for reporting serious breaches).

#### Reporting of serious breaches

A ‘serious breach’ is defined as a breach of GCP or the trial protocol which is likely to affect to a significant degree:The safety or physical or mental integrity of the subjects of the trial; orThe scientific value of the trial

In the event that a serious breach is suspected, the NHSBT CTU must be contacted within one working day. In collaboration with the chief investigator and the DMC, the serious breach will be reviewed by the NHSBT CTU. If appropriate, NHSBT CTU, in conjunction with the sponsor, will report it to the REC committee and the host institution within seven calendar days.

### Plans for communicating important protocol amendments to relevant parties (e.g. trial participants, ethical committees) {25}

In the event of protocol amendments by the investigator, notification to the trial management group and NIHR (funder is required). In addition, the amendment documents and associated amendment tool is completed and sent to the sponsor for review and approval. Following sponsor approval, the amendment documents are submitted to the research ethics committee (REC) for authorisation. Amendments can only be implemented if a favourable opinion is granted by the REC.

## Dissemination plans {31a}

### Data analysis and release of results

By conducting the study, the local investigators agree that all information provided by the sponsor and co-ordinating centre will be maintained by the local investigators and the site personnel in strict confidence. It is understood that the confidential information provided to local investigators will not be disclosed to others without authorization from the sponsor and/or co-ordinating centre.

The scientific integrity of the study requires that all data must be analysed study-wide and reported as such. No data from the study will be presented in oral or written form without permission of the TSC. Approval to submit papers for publication will include all authors of the paper.

### Primary outcome publications

All publications, abstracts and other outputs will be reviewed by the trial steering committee (TSC) prior to publication. Publications will reflect the input of all participating centres in authorship, which will be agreed by the TSC.

Reports relating to primary outcomes will be published in peer-reviewed journals of appropriate relevance. Individual centres will undertake not to report any trial data independently. A final report on the primary outcomes of the study will be compiled by the chief investigator and NHSBT CTU and approved and signed off by each local investigator.

### Other study papers, abstracts and presentations

Study investigators wishing to publish secondary data analyses will submit a proposal to the TSC for approval. If the committee accepts the proposal, then the author of the proposal may decide on the lead in each publication resulting from such a proposal.

### Identification

The ISRCTN trial identifier will be included on all presentations and publications.

### Lay summary

Liver disease is the third leading cause of premature death in the UK. Liver transplantation is the only successful treatment for end-stage liver disease but is limited by a shortage of suitable donor organs. As a result, up to 20% of patients on the NHS liver transplant waiting list die before receiving a lifesaving transplant. However, a third of donated livers cannot be used for transplants. A frequent reason for this is the presence of fat within the liver cells (known as non-alcoholic fatty liver disease). This affects a third of the UK population and is commonest with obesity. As the incidence of obesity in the general population increases, donated organs are more likely to be fatty.

Transplanting a fatty liver carries a much greater risk to the patient compared to a normal liver. This is because fatty livers do not tolerate being cooled down, and we currently store organs in an ice box before the transplant. An alternative new technology (normothermic machine perfusion; NMP) stores the liver in very similar conditions to those in the body: it maintains the liver at body temperature and provides oxygen and nutrition. We know that this preserves it in better condition, with less damage to liver cells: it also allows the surgeon to test how well the organ is working before deciding whether to carry out the transplant. However, whilst beneficial, NMP technology does not completely resolve the problem of fatty livers, because fat remains in the liver cells.

We have been testing a new way to remove fat from the liver during NMP. We add a combination of (currently available) drugs to release fat from liver cells, and we remove the fat from the perfusion machine using a filter. This reduces the amount of fat in the liver and improves its function. None of the livers treated in this experimental study were actually transplanted: if used for patients, we believe that this might increase the number of livers that could be transplanted safely.

In the proposed trial, we will randomly assign 60 livers from donors with a high risk of fatty liver disease to either NMP alone or NMP with fat removal treatment. We will assess how many of these livers are safe to transplant and, in those that are transplanted, follow the outcomes after the operation. The main objective is to show whether this treatment is safe; it will also help us to design a future, larger study which will test the extent to which fat removal actually leads to additional transplants.

Patients and their families have contributed in the design of the study and will be members of the committee that run it. They believe that the study is addressing an important issue, particularly in the context of the global obesity crisis and its consequent implications for liver transplantation. They have concluded that this area of research is of great significance in order to reduce waiting list deaths.

## Discussion

This study addresses the paradox whereby patients die on the liver transplant waiting list whilst less than two thirds of deceased donors result in a transplanted liver in the UK. Poor utilisation of steatotic livers is exacerbated by the globally increasing incidence of obesity and the associated increase in frequency of hepatic steatosis in donors. If the benefit of NMP with ex-situ treatment of steatotic livers are confirmed, NHS practice will be influenced with much greater utilisation of moderately and severely steatotic organs. Evidence that supports this hypothesis is the primary purpose of this study.

More broadly, this research has the potential to move NMP into the realm of targeted interventions, i.e. ex-situ pharmacological optimisation of a donor organ prior to transplantation. However, there are number of considerations that will determine the success of this study.

### Potential barriers to research

#### Regulatory

The pharmacological agents that form an important part of the basis of this proposal, although readily available for patient use, are not licensed for this application. The MHRA has reviewed our application and advised that our proposal is not a clinical trial of an Investigational Medicinal Product (IMP) as defined by the EU Directive 2001/20/EC and no submission to the Clinical Trials Unit at the MHRA is required. This outcome has been in the context of a previous comparable negotiation between OrganOx Ltd. and the MHRA, over the use of sodium taurocholate. This is a choleretic agent, a bile salt of bovine origin, that is used to optimise biliary function in perfused livers and infused continuously throughout perfusion. The MHRA agreed that the flushing of the liver at the end of perfusion (with 2 L of preservation solution) resulted in below therapeutic levels of sodium taurocholate carried to the patient.

#### Cost

We are not proposing to carry out heath economic analysis as part of the proposed trial, but data collection is being planned in another NMP trial. In general, transplantation is highly cost-effective and it is expected that the cost of technology that increases the productivity of transplant units will fall below the NICE threshold of £20,000 per QALY.

#### Complexity

As noted above, all seven UK liver transplant centres have access to the OrganOx NMP system and have technical teams that are trained in its use. The additional skills to implement the defatting protocol, beyond those of NMP alone, will be well within the skill-set of the teams, with some specific extra training. NMP is increasingly used for steatotic livers, especially the moderately and severely steatotic organs that form the target for this technology, and so the additional complexity involved in adding the defatting protocol will be small. The evolution of objective criteria to determine transplantability will be a welcome benefit to clinical teams—this is a very difficult and high-stakes judgement which is currently made with limited information.

#### Priority

The perceived importance of this research is high: at the recent annual conference of the British Transplantation Society, a ‘Dragon’s Den’ session interrogated a number of proposed research initiatives, including NMP defatting. This was very highly rated in terms of both interest and importance. Utilisation of currently discarded organs is seen as probably the most pressing individual challenge in liver transplantation today. Indeed, patients are much more likely to die on the waiting list in the UK (as a result of the organ donor shortage) than in the year after their transplant.

### Adoption of technology

The powerful need to improve the utilisation of steatotic organs is recognised by patients (who are aware of the mortality rate on the waiting list, as well as the restrictions on waiting list access) and healthcare providers (both transplant teams and NHS Trusts), who are anxious to increase transplant rates for reasons of both patient benefit and unit efficiency. There are, therefore, both ‘push’ and ‘pull’ factors that will encourage the adoption of any new technology that enables safe transplantation of moderate/severely steatotic livers.

Adoption of technology of this sort attracts a high level of publicity within the wider public and media, mainly because of its obvious life-saving connotations. For this reason, it is likely to attract political attention. Much political support for organ donation and transplantation over the last 10 years has resulted in a greatly increased donation rate and the recent implementation of the ‘opting-out’ system of consent has further raised the profile of transplantation both politically and in the community.

The technical barriers to adoption are surmountable, particularly as liver NMP is now available in all seven UK liver transplant centres; the addition of defatting is technically well within the capabilities of clinical teams skilled in the operation of existing NMP. The underlying technology is CE marked; in January 2019, NICE approved the use of ex-situ machine perfusion for extracorporeal preservation livers for transplantation (with special arrangements for clinical governance).

There is a good track record in the implementation of novel techniques within transplantation in the UK. NHSBT (blood and transplant) is very supportive not only of translational research (such as the proposed study) but also of the adoption of novel therapies: indeed, one of the advisory groups to NHSBT, the ‘Research and Innovation Advisory Group’, was established with precisely this objective.

